**Methods/design:**

A single-blind randomized clinical trial comprising 90 adolescents with PTSD using a permuted block design will be utilized. Nurses previously naïve to prolonged exposure and supportive counselling will be trained to provide these treatments at the adolescents’ high schools. Data collection will last from March 2014 to December 2017 and annually thereafter, dependent on the availability of funding.

Participants will receive seven to fourteen 60 min sessions of prolonged exposure treatment (*n* = 45) or supportive counselling (*n* = 45). All assessments will be conducted before treatment, at mid-treatment, immediately after treatment completion, at 3-, 6-, and 12-month follow-up, and annually thereafter. It is hypothesized that PE-A will be superior to SC in reducing PTSD symptoms at post-treatment as measured by the CPSS-I administered by an independent evaluator. It is further hypothesized that PE-A treatment gains will be maintained at 3-, 6- and 12-month follow-ups and annually thereafter.

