**Fig. 1 Fig1:**
[figure not shown]
Study Consort Diagram, Consort diagram

A single-blind permuted block randomized control design will be used. The proposed research aims to examine the effectiveness of a psychotherapeutic intervention administered by counsellors to treat the symptoms of PTSD in adolescents exposed to trauma. The aim is to conduct a randomized controlled trial (RCT) to compare PE-A to SC to determine the comparative effectiveness in reducing PTSD and associated symptoms in adolescents.

The study will compare the efficacy of PE-A to SC. Participation will be voluntary. All participants, who meet full PTSD or sub-threshold PTSD criteria, will be scheduled for a pre-treatment assessment with Independent Evaluators (IE). The one IE will be an experienced diagnostician and clinical psychologist and the other an experienced psychiatric nurse. Adolescents will be randomly assigned on a 1:1 ratio to receive either PE-A or SC.

Treatment will consist of 7–14 sessions of either PE or SC. The number of sessions each participant receives will be based on the weekly self-report measure of PTSD symptoms (Child PTSD Symptom Scale – Self Report; CPSS-SR); however, this will range between a minimum of 7 sessions to a maximum of 14 sessions. A 70% symptom reduction is chosen as sufficient for treatment termination.

After session five, all participants will receive a mid-treatment evaluation by the IE. The IE will again assess the participants upon termination of treatment. Participants will then enter the non-treatment follow-up phase. Participants who prematurely terminate therapy (before 70% symptom reduction or 7 sessions) will undergo a post-last session assessment with the IE and will then enter the follow-up phase. Follow-up assessments will be conducted at 3-, 6-, and 12 months post-treatment and annually thereafter. The IE assessments will comprise both structured clinical interviews and self-report measures. The assessments will cover PTSD severity, related psychopathology, general psychopathology, and PTSD-related cognitions. At the 12-month follow-up, participants who receive SC and are deemed to still have clinically significant PTSD symptoms (as determined by the IE at 12-month follow-up assessment), will be offered PE-A. To add to the rigor of the study and demonstrate the long-term efficacy of the intervention, there will be annual posttreatment follow ups, dependent on the availability of funds for this purpose.

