A cross-sectional qualitative evaluation will take place during the follow up assessments of the adolescents who have completed their treatment. Adolescents who participated in the study in the preceding year (regardless of completion or outcome) will be invited to participate in semi-structured interviews with an independent psychologist. Similarly, there will also be separate focus groups for the nurse counsellors and the contact persons at the schools who had been part of the study during the preceding year.

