The CPSS-SR will be administered at the beginning of each session in order to monitor treatment progress. From session 7, the percentage improvement from the pre-treatment baseline will be measured. When improvement reaches 70% or better, the counsellor will share the outcome with the participant and start the termination process.

The follow-up assessments will be administered by an IE blind to the treatment condition.

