#### Qualitative portion of study

Adolescents who agree to participate in the study will be interviewed by an independent evaluator and will participate in a treatment specific focus group. These interviews will be audio-recorded.

The focus groups with the nurse counsellors and school contact personnel will be conducted at Stellenbosch University by an independent clinical psychologist. A co-facilitator will record field notes and manage the audio-recording.

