### Measures

A pilot study of 12 participants [38] was used to determine the final assessment battery (from the included battery) that will be used for the study. The pilot study was also used to identify any logistical or treatment protocol implementation difficulties.

The assessment battery that will be administered to all adolescents who are eligible on screening is detailed below in Table 3.

**Table 3 Tab3:** Measures used in assessment, Measures used and indication when used in assessment

Domain	Measure	Assessing	Informant	Time (min)	Pre T1	Mid T2	Post T3	3, 6, 12 month FUs
Diagnostic Information	MINI-KID [45]	PTSD and other symptoms	*IE*	90	X			
	MRC Demographic Questionnaire	Demographic Information	*Parent*	10				
Psychopathology	CPSS [46, 47]	PTSD severity	*IE*	10	X	X	X	X
	CGAS [48]	*General Functioning*	*IE*	*5*	X	*X*	*X*	*X*
	BDI [49, 50]	*Depression*	*Adolescent*	*10*	X	*X*	*X*	*X*
	STAXI [51, 52]	*Anger*	*Adolescent*	*10*	X	*X*	*X*	*X*
	CBCL-YSR [53]	*General psychopathology*	*Adolescent*	*20*	X		*X*	*X*
	MASC [54, 55]	*Anxiety*	*Adolescent*	*5*	X	*X*	*X*	*X*
	PESQ [56]	*Substance use*	*Adolescent*	*15*	X	*X*	*X*	*X*
Cognition & Emotion	C-PTAS [57]	Trauma-related cognitions	*Adolescent*	10	X	X	X	X
	CAPS [58]	Attributions and perceptions	*Adolescent*	10	X	X	X	X
	PTCI [66]	Trauma-related cognitions	*Parent*	10	X		X	X
	NMR [59, 60]	Affect Regulation	*Adolescent*	10	X		X	X
	MSPSS [61, 62]	Social support	*Adolescent*	10	X	X	X	X
	Rosenberg [63]	Self-esteem	*Adolescent*	3	X	X	X	X
	CD-RISC [64]	Resilience	*Adolescent*	5	X	X	X	X
Symptoms – Parents	PDS [65]	PTSD	*Parent*	20	X		X	X
	BDI [49, 50]	Depression	*Parent*	10	X		X	X
Treatment variables	Expectancy-A	Tx expectancy	*Adolescent*	2	X			
	Satisfaction-A	Tx Satisfaction	*Adolescent*	2		X	X	X
	CPSS [41]	PTSD severity	*Adolescent*	10	Every session			
	Treatment compliance	Compliance with the treatment	*Therapist*	2		X	X	X

All measures will be obtained by an IE at baseline, mid-treatment (after 5 sessions), and post-treatment, and again at 3-month, 6-month and 12-month follow-up, and in following years at annual intervals, dependent on the availability of funds.

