#### Psychopathology measures

##### *The Child PTSD Symptom Scale–Interview (CPSS-I*; [46]*)*

The CPSS-I will be used in conjunction with the MINI-KID to assess PTSD diagnosis and PTSD symptom severity. The CPSS interview (8–18 years), is based on DSM-IV criteria and provide a Total-, re-experiencing-, avoidance- and hyperarousal score. The CPSS-I has 17 items that correspond with the DSM-IV and an additional 7 items. The CPSS-I Total score ranges from 0 to 51 and each item is rated from 0 to 3. Internal consistency ranged from .70–.89 for the total and symptom cluster scores. Test-retest reliability was good to excellent (.84 for the total severity score, .85 for re-experiencing, .63 for avoidance and .76 for arousal). Convergent validity was high (.80) between the CPSS and the Child Posttraumatic Stress Reaction Index [47]. A cutoff Total score of 11 or higher on the CPSS yielded 95% sensitivity and 96% specificity of diagnosis. The CPSS-I Total Score will be used as the primary outcome measure.

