All study data will be confidential. The following steps will be taken to minimize risks to confidentiality: a) evaluation protocols and treatment record forms will be kept in locked cabinets in the IE office; b) participant identity will be disguised using ID numbers keyed to a master list; c) all recordings will be transferred to removable storage that will be kept in locked storage in locked rooms; d) data will be entered directly onto computer files that will be password protected; and e) computer files will carry only participant numbers for case identification. All project staff will be trained in the importance of confidentiality. If the results of the study are published, data that might reveal the identity of a participant will be disguised.

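### Treatment records are stored in the office of the evaluators who score the CPSS-I, and the explicit blinding sentence does not reach the post-treatment primary rating

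*Protocol article*

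**What the plan says.** All references are to the Protocol article.

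- **Storage.** The first of the confidentiality steps under Protection against risks reads: "evaluation protocols and treatment record forms will be kept in locked cabinets in the IE office".
- **Primary outcome and rater.** The section on the CPSS-I says "The CPSS-I Total Score will be used as the primary outcome measure". The abstract (Methods/design) gives the hypothesis: "PE-A will be superior to SC in reducing PTSD symptoms at post-treatment as measured by the CPSS-I administered by an independent evaluator".
- **Post-treatment assessment.** Design says "The IE will again assess the participants upon termination of treatment". That sentence does not mention blinding.
- **Evaluator blinding.** The abstract and Design call the trial single-blind without naming who is blind. The only sentence that attaches blindness to an evaluator is in Procedure: "The follow-up assessments will be administered by an IE blind to the treatment condition".
- **Allocation.** Under Procedure, only the project coordinator can see the randomisation scheme. The coordinator tells the counsellor which arm a participant is in.
- **Qualitative interviewer.** Qualitative portion of study says that adolescents "will be interviewed by an independent evaluator and will participate in a treatment specific focus group". Design gives the interviewer as an independent psychologist, and Protection against risks as a clinical psychologist. On timing, Design says "A cross-sectional qualitative evaluation will take place during the follow up assessments of the adolescents".

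**The concern.** The CPSS-I is scored by an interviewer, so a rater who knows the arm can let expectation influence the score. Counsellors know the treatment they deliver, and participants are given the rationale of the treatment they receive. That leaves the IE's blindness as the only stated protection of the primary comparison against this kind of bias.

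The article protects that blindness at one point by restricting the randomisation scheme to the coordinator. It weakens it at another by placing the session paperwork in the raters' own office. The sentence that should settle the matter names follow-up assessments and leaves out the visit at which superiority is tested. If PE-A came out ahead, a critic could ask whether the raters knew the arm, and the article as written would give no firm answer.

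**Working it through.** No figure in the plan bears on this point, so the check sets the sections side by side.

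1. **Who is the blinded party?** Procedure has the counsellor informed of the arm. The descriptions of both treatments, with Tables 1 and 2, have the adolescent given the treatment rationale. In a single-blind trial with an independent evaluator, only the IE is left as the blinded party.

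2. **Which ratings depend on it?** The IE makes the CPSS-I rating before treatment, after session five, at the end of treatment and at each follow-up. No treatment record exists at the first of these. The others are all open to the problem, including the post-treatment rating that carries the primary hypothesis.

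3. **Would the records reveal the arm?** The article does not list what the treatment record forms contain, so this is an inference. It is a strong one. Under The SC treatment group, counsellors note when the trauma is discussed and for how long, and Monitoring treatment integrity also asks for such notes in SC sessions. PE-A is built on an in vivo hierarchy and repeated imaginal exposure. An ordinary session record from either arm would be hard to mistake for the other.

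4. **Does anything stop the IE from seeing them?** The cabinets are locked, but the lock is listed as a safeguard for participant confidentiality. The article does not say who holds the keys and states no rule that keeps the IEs out. Participant numbers in place of names do not help, because the rater must know which participant is being rated.

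5. **What does the blinding sentence cover?** Design separates three things: the evaluation after session five, the assessment when treatment ends, and a later follow-up phase at 3, 6 and 12 months and annually. The Procedure sentence uses the term follow-up. Read with Design, it leaves out the mid-treatment and post-treatment ratings.

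6. **Could the qualitative interview unblind a rater?** The three descriptions of the interviewer do not agree. Design says that one of the two IEs is a clinical psychologist, so none of the three wordings rules out a rating IE. The interviews fall in the follow-up period, after the post-treatment rating. They could affect only later CPSS-I ratings, which serve the hypothesis that gains are maintained, and only if the interviewer also rates.

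**Size.** A numerical bias would need a between-participant SD of the CPSS-I and an assumed shift in ratings among unblinded evaluators. The article gives neither, so no figure is offered.

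**The case against.** The strongest reply is that this is a condensed article. Access to cabinets is normally settled in the full protocol or operating procedures, the cabinets are locked, and the contents of the forms are not described. Procedure also gives each counsellor a file on every participant, and nothing says when paperwork moves to the IE office. It might arrive only after the ratings are complete.

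Part of this stands. The missing access rule is not itself a fault of the article, and the content of the forms is inferred. But the location is stated, it is the raters' office, and no time limit is attached. That sits badly with single-blinding whatever the fuller documents add.

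Three stronger readings are tempting and are not supported:

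- **That post-treatment ratings are unblinded.** A reader might infer this from the Procedure sentence. However, the whole trial is declared single-blind, and the rationale section commits to independent evaluators for outcome assessment. The sentence is too narrow; it does not declare any rating open.
- **That the qualitative interview contaminates the primary rating.** It comes after that rating, so it cannot.
- **That the compliance and satisfaction forms unblind the IE.** Measures says "All measures will be obtained by an IE at baseline, mid-treatment (after 5 sessions), and post-treatment", and Table 3 includes both items. They are generic five-point scales that do not name a treatment. SC also has between-session work, the daily diary, so a homework rating does not identify PE-A. The general sentence cannot be wholly literal either, since Table 3 has the self-report CPSS completed at every session and names the therapist as informant for compliance.

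**Conclusion.** The point holds in a limited form. The stated storage place for treatment records conflicts with the blinding of the evaluators who score the primary outcome, and the explicit blinding sentence does not name the primary time point. The first opens a possible route to unblinding at every CPSS-I rating after treatment begins. The second is a wording gap that the single-blind label only partly covers. The inconsistent description of the qualitative interviewer is minor and concerns the later maintenance ratings alone.

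This rests on two assumptions: that treatment record forms describe session content well enough to show the arm, and that the IEs can open cabinets in their own office. Both are plausible and neither is stated. The documents show an avoidable opportunity for unblinding; they do not show that it happened, and its effect on the result cannot be sized from them. It is worth correcting because the remedy is cheap and protects the primary rating. It is not a ground for calling the primary result invalid.

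**What to change.** - **Protection against risks:** keep only evaluation forms in the IE office. Hold treatment records where the IEs have no access, for example with the project coordinator, who already holds the allocation.
- **Procedure:** reword the blinding sentence so that the IE is blind to treatment condition at the mid-treatment, post-treatment and follow-up assessments.
- **Design, Qualitative portion of study and Protection against risks (minor):** describe the qualitative interviewer in the same way in all three places, and state that this person does not rate outcomes in the trial.
- **Ratings already made under the present arrangement:** report who had access to the cabinets.

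The cost is a change of storage place, slightly more handling by the coordinator and a few reworded sentences. No additional assessment is needed, and the analysis does not change.

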### Data safety and monitoring review board

In view of the potentially high risks associated with counsellors administering psychotherapeutic interventions in a vulnerable population (traumatized adolescents with PTSD), a Data Safety and Monitoring Board (DSMB) will be established for this trial. The DSMB will include a child psychiatrist, clinical psychologist, statistician and an ethicist. The DSMB will meet at regular intervals upon completion of the pilot study, as well as every 6 months during the study, to review cumulative data and to evaluate the safety of human participants, study conduct, and the scientific validity and integrity of the data. The DSMB will report back on its findings to the study team and to the Health Research Ethics Committee (Faculty of Health Sciences, Stellenbosch University) via the Principal Investigator. Audio-recordings will be stored in a locked cabinet in the researcher’s office and destroyed after 5 years.

### Study implications

Information from this study can directly inform and benefit both policy makers and participants by guiding appropriate treatment planning and providing some therapeutic answers to a population in need. Thus, if the hypotheses of this study are supported by the data, dissemination of these treatments, to be delivered by trained and supervised previously psychotherapy-naïve health care personnel in general practice would be recommended. Participants in the treatment study will benefit from receiving well-delivered treatment for PTSD and the task-shifted counsellors will benefit from learning evidence-based effective treatments for PTSD under close and supportive supervision. Participants may also benefit from knowing that they have contributed to the scientific understanding of PTSD and its treatment that may help other adolescents struggling with similar problems and their community care providers.

## Abbreviations

BDI: Beck Depression Inventory
CAPS: Children’s Attributions and Perceptions Scale
CBCL: Child Behavior Checklist
CBT: Cognitive behavior therapy
CCT: Child-centered Counseling
CD-RISC: The Connor-Davidson Resilience scale
CGAS: Children's Global Assessment Scale
CPSS: Child PTSD Symptom Scale
C-PTAS: Child Post-Trauma Attitudes Scale
CSA: Childhood sexual assault
DSMB: Data Safety and Monitoring Board
GEE: Generalized estimating eqs.
IE: Independent Evaluator
LMM: Linear mixed-effects model
MASC: The Multidimensional Anxiety Scale for Children
MINI-KID: Mini International Neuropsychiatric Interview for Children and Adolescents
MRC: Medical Research Council
MSPSS: Multidimensional Scale of Perceived Social Support
NMR: Negative Mood Regulation
NSHW’s: Non-specialized primary care health workers (NSHW’s)
PDS: The Posttraumatic Stress Diagnostic Scale
PE: Prolonged exposure
PE-A: Prolonged Exposure for Adolescents
PESQ: Personal Experience Screening Questionnaire
PTCI: Posttraumatic Cognitions Inventory
PTSD: Posttraumatic Stress Disorder
RCT: Randomized control trials
SC: Supportive Counselling
SEM: Structural equations models
SOP: Standard operating procedure
STAI: State-Trait Anxiety Inventory
STAXI: The State-Trait Anger Expression Inventory
TF-CBT: Trauma-Focused Cognitive Behavioral Therapy
WCED: Western Cape Education Department
